#### Anthropometric measures

At the beginning and end of the study, data will be collected regarding anthropometric measurements, including height, weight, BMI, and WC. Body weight will be measured in a fasted state, wearing minimal clothing and without shoes, using a digital scale with a precision of 100 g. WC will be measured using a measuring tape, measuring the distance between the suprailiac bone and the last rib with a precision of 0.5 cm. Standing height will be measured using a standard stadiometer without shoes, with a precision of 0.5 cm. BMI will be calculated using the measured height and weight (weight in kilograms/height in square meters) [28].

### Statistical analysis

Statistical data will be analyzed using SPSS software version 22. The results will be reported as mean ± standard deviation (SD). The normality of variable distributions will be checked using the Kolmogorov–Smirnov test. If a variable does not follow a normal distribution, a logarithmic transformation will be applied. The independent t-test will be used to compare the consumption of food and nutrients between the two groups, and the chi-square test will be used to compare qualitative variables between the two groups. The analyses will be performed based on the intention-to-treat (ITT) approach. Missing values will be treated according to the linear regression method. ANCOVA with adjustment with baseline values will be used to assess the effect of intervention on dependent variables. *p*-value < 0.05 will be considered statistically significant.

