### Participants

Participants with NAFLD will be recruited based on the inclusion criteria. NAFLD will be diagnosed according to the Fibro Scan (Metavir-score ≤ F2 and controlled attenuation parameter (Cap) score > 263). To better reflect population diversity and obtain more generalizable results, individuals will be recruited through popular online advertising applications.

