### Sample size calculation

To compare the studied variables between the two groups, considering the error of 5%, the power of 80%, and the effect size of 0.8 (based on Cohen's criterion), the minimum sample size is equal to 26 people in each group and a total of 52 people will be determined.

*t tests—Means*: Difference between two independent means (two groups)

*Analysis:* A priori: Compute required sample size

*Input:* Tail(s) = Two

Effect size d = 0.80

α err prob = 0.05

Power (1-β err prob) = 0.8

Allocation ratio N2/N1 = 1

*Output*

Noncentrality parameter δ = 2.8844410

Critical t = 2.0085591

Df = 50

Sample size group 1 = 26

Sample size group 2 = 26

Total sample size = 52

Actual power = 0.8074866

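### A normality test on the raw variables, run after the data are seen, decides whether each continuous outcome is analysed as a difference or a ratio, and the only named summary, mean ± SD, does not fit the log scale

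*Protocol article*

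**What the plan says.** All the relevant text is in the Statistical analysis section of the protocol article.

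- Check: "The normality of variable distributions will be checked using the Kolmogorov–Smirnov test".
- Action: "If a variable does not follow a normal distribution, a logarithmic transformation will be applied".
- Summary: "The results will be reported as mean ± standard deviation (SD", given as a general convention with no exception for transformed variables.
- Treatment effect: "ANCOVA with adjustment with baseline values will be used to assess the effect of intervention on dependent variables".

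No outcome has its scale named in advance, and residuals are not mentioned. The article does not say whether the test is run per arm or pooled, at baseline or at week 12, or with the Lilliefors correction for an estimated mean and SD. Under Primary and secondary outcome, the continuous outcomes include ALT, AST, GGT, fasting insulin, HOMA-IR and triglycerides, besides the FibroScan measures.

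**The concern.** There are three defects in the rule as stated.

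1. **It tests the wrong object.** ANCOVA needs reasonably behaved residuals. It does not need a normal raw outcome, and it asks nothing of the distribution of the baseline covariate.
2. **The effect measure is not fixed.** On the original scale the treatment effect is a difference in means; on the log scale it is a ratio of geometric means. A p-value computed after the data are in chooses between them, outcome by outcome. Because the variant of the test is open, two analysts who both follow the text can report different effect measures for the same outcome.
3. **The summary does not fit.** An arithmetic mean ± SD in each arm does not correspond to a log-scale ANCOVA, whose natural summary is the geometric mean.

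At stake are some power on skewed outcomes and a clear reading of the results. In a trial of 52 people, the choice of scale can also move an outcome across p = 0.05.

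**Working it through.** **The plan's own figure.** Inputs from Sample size calculation: "Effect size d = 0.80", "α err prob = 0.05" two-sided, "Power (1-β err prob) = 0.8", 26 per group.

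- Noncentrality = 0.8 × √(26/2) = 2.8844; df = 50; critical t = 2.0086.
- Power from the noncentral t = 0.8075, as stated. With 25 per group it is 0.791, so 26 is the minimum.

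The sample size is right for its inputs, and this point does not affect it.

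**Assumptions.** The documents give no SD, CV or skewness. Outcomes are taken as lognormal, with raw-scale CV = √(exp(σ²) − 1) for log-SD σ. Log-SD 0.5 gives CV √(exp(0.25) − 1) = 0.53, and 0.6 gives √(exp(0.36) − 1) = 0.66.

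**How often the test leaves a lognormal outcome untransformed** (20,000 runs, 5% level). The approximate critical distances at n = 52 are 0.122 (Lilliefors) and 0.185 (uncorrected).

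| CV | n = 52, Lilliefors | n = 52, uncorrected | n = 26, Lilliefors | n = 26, uncorrected |
|---|---|---|---|---|
| 0.3 | 66% | 99% | 82% | over 99% |
| 0.5 | 32% | 90% | 61% | 98% |
| 0.8 | 7% | 59% | 33% | 90% |
| 1.0 | 2% | 38% | 21% | 81% |

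The scale chosen depends heavily on details that the text leaves open.

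**Power of the rule as written.** On the log scale, follow-up = ρ × baseline + σ√(1 − ρ²) × error − δ × arm, with δ = 0.8 × σ√(1 − ρ²), that is, 0.8 residual SD. With ρ = 0.6 and σ = 0.5, δ = 0.8 × 0.5 × 0.8 = 0.32. ANCOVA uses 26 per arm and 49 residual df. The test is pooled at n = 52; 8,000 runs. Ranges span the ways of applying the pooled test that were tried.

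| Log-SD | Log fixed in advance | Always raw | Rule, Lilliefors | Rule, uncorrected |
|---|---|---|---|---|
| 0.5 | 79.7% | 73.5% | 78.8–79.5% | 74.6–75.2% |
| 0.6 | 79.5% | 70.0% | 78.6–79.4% | 73.3–74.9% |

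Loss against the fixed log scale:

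- Lilliefors: 79.7 − 79.5 = 0.2 to 79.7 − 78.8 = 0.9 points at log-SD 0.5, and 0.1 to 0.9 at 0.6.
- Uncorrected: 79.7 − 75.2 = 4.5 to 79.7 − 74.6 = 5.1 points at log-SD 0.5, and 4.6 to 6.2 at 0.6.

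A repeat with 40,000 runs, letting the baseline test, the follow-up test or either of them set the scale, gave losses of 0.1–1.8 points (Lilliefors) and 4.5–6.9 points (uncorrected). Hence the rounded figures of about 1 and about 5–7.

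**Wider range** (20,000 runs, baseline correlation 0.5 and 0.7, pooled test, scale set at follow-up; fixed log about 0.80 throughout).

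| CV | Always raw | Rule, Lilliefors | Rule, uncorrected | Raw and log disagree on p < 0.05 |
|---|---|---|---|---|
| 0.3 | 0.77 | 0.78 | 0.77 | about 6% |
| 0.5 | 0.73–0.75 | 0.78–0.79 | 0.74–0.75 | 10–11% |
| 0.8 | 0.66–0.68 | 0.80 | 0.74–0.75 | 16–19% |

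At log-SD 0.5–0.6 and correlation 0.6 the disagreement is about 11–14%. All disagreement figures are with a true effect present. Type I error is 0.046–0.054 in every variant.

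**The case against.** The strongest reply is that this is a condensed article. Back-transformation, residual checks, confidence intervals and a list of scales commonly sit in a full protocol or SAP, and the rule does little damage. The first part would answer a complaint about missing detail. It does not answer this one, because the article states a complete rule and it is the rule that is faulty. The second part stands in large measure: with a pooled Lilliefors test the power cost is about 1 point, and false positives are not inflated.

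Several stronger readings are tempting, but the documents do not support them.

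- **A loss of some 6 to 10 points of power.** That compares a fixed log scale with an analysis that never transforms (79.7 − 73.5 = 6.2; 79.5 − 70.0 = 9.5). The article does transform when the test rejects.
- **Skewed outcomes are often analysed on the wrong scale.** No SD or skewness is given. The claim is true for mild to moderate skew under some variants of the test, and false for strong skew with a pooled Lilliefors test, which misses only 2–7% at CV 0.8–1.0.
- **At least one truly normal outcome would probably be logged.** With 17 outcomes, 1 − 0.95^17 = 0.58. This assumes independence and normality of all 17, but HOMA-IR and QUICKI are functions of insulin and glucose, and BMI of weight and height. An uncorrected test almost never flags a normal variable.
- **Baseline CAP breaks the model.** Entry requires "controlled attenuation parameter (Cap) score > 263", so baseline values are truncated by design. Baseline CAP is a covariate, however, and ANCOVA does not need it to be normal.
- **Baseline and follow-up end up on different scales.** This could happen if each time point were tested and transformed separately, but the text does not say so.
- **Mean ± SD is a step after the transformation.** It is a general convention; the defect is only that it makes no exception for logged variables.

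The rule also does not reach every outcome. Qualitative variables go to a chi-square test, and fibrosis stage is categorical.

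**Conclusion.** The point holds in a limited form. As written, a K–S test on raw variables rather than residuals chooses the scale after the data are seen. The effect measure of each continuous outcome is therefore not fixed in advance, and the only named summary does not match a log-scale analysis. These statements follow from the text and need no assumption.

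The size of the harm does rest on assumptions: lognormal outcomes, log-SD 0.5–0.6, baseline correlation 0.6, 26 per arm, no missing data. Under these, the rule costs about 1 point of power with the Lilliefors correction and about 5–7 points without it. Type I error stays near 5%. With a true effect, raw and log ANCOVA disagree on significance in about 11–14% of trials, so fixing the scale can change a reported result. The harm is moderate at most, but the remedy is nearly free and should be adopted.

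**What to change.** Replace the K–S rule with a scale named for each continuous outcome before outcome data are seen, the same for baseline and follow-up. A workable starting list is log for triglycerides, insulin, HOMA-IR, ALT, AST, GGT and liver stiffness, and original units for the rest. The documents hold no distributional data to settle this, so the final list is for the trial statistician.

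Check the ANCOVA residuals, not the raw variables. Beside the arm summaries, report the adjusted mean difference with its 95% CI; for log-scale outcomes, report geometric means and their adjusted ratio with its 95% CI. Heteroscedasticity-robust (HC3) errors or a permutation test are optional as sensitivity analyses.

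Cost: two or three sentences in the analysis section, with no new data and no change to the sample size. The downside is that log-scale results have to be read as ratios.

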### Intervention

Participants will be randomly assigned to either intervention or control group. During the conversation with the patients, each patient will be assigned to either the IF diet or the LCD. Individuals in the intervention group will follow a 16:8 IF diet that will allow them to consume only water and non-energy beverages such as tea, coffee, and sugar-free chewing gum for 16 h and eat food ad libitum for 8 h. The control group will receive LCD with 3 main dishes and 3 snacks with 55% carbohydrate, 30% fat, and 15% protein (300 kcal less than energy requirements) for 12 weeks.

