### Compliance

Participants' food intake will be recorded every week to assess how well they are adhering to their diet. Participants will complete a total of 12 food records. Patients will be requested to report their dietary intakes using home measurements to complete their daily recall. Finally, home measurements will be converted to grams using the brochure provided. Participants' total food intake will be examined using the average of all meal recalls during the intervention period. We will calculate energy intake, micronutrients, and macronutrients from dietary recalls using Nutrition IV software (First Databank, San Bruno, CA, USA) modified for Iranian meals. Text messages will be sent to patients to increase diet compliance and remind them to follow the diet.

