#### Assessment of dietary intake

As mentioned above, dietary intake will be assessed using 24-h dietary recall (including one weekend day and two working days) at baseline, weeks four, eight, and twelve of the intervention. Experienced and trained professionals will collect these recalls from the participants, and the mean intake of food items during these four recalls will be calculated in grams per day. The nutrient intake of individuals will be calculated using N4 software (Nutritionist4).

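### Food and nutrient intake is compared by an unadjusted t-test although baseline intake is collected; the test is valid, but baseline-adjusted ANCOVA would be more precise at almost no cost

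*Protocol article*

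**What the plan says.** The Statistical analysis section gives intake its own test: "The independent t-test will be used to compare the consumption of food and nutrients between the two groups". For intervention effects it states a different method: "ANCOVA with adjustment with baseline values will be used to assess the effect of intervention on dependent variables".

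Assessment of dietary intake says that recalls are taken "at baseline, weeks four, eight, and twelve of the intervention", so each participant has a pre-diet value from the same instrument. It then says "the mean intake of food items during these four recalls will be calculated in grams per day", which puts the baseline recall into the mean. The Compliance section describes a different summary: "Participants' total food intake will be examined using the average of all meal recalls during the intervention period". It gives the purpose as adherence: "Participants' food intake will be recorded every week to assess how well they are adhering to their diet".

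Under Intervention, the fasting arm may "eat food ad libitum for 8 h", while the control diet is set at "300 kcal less than energy requirements". The list of primary and secondary outcomes does not include intake.

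**The concern.** The covariate exists and the plan uses the matching method elsewhere, yet the test named for intake ignores it. People differ in habitual intake, and some of that difference persists on a diet. A t-test on on-diet intake leaves the persistent part in the error term. If the arms happen to differ at baseline, that observed difference also passes into the estimate in proportion to r.

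The arms differ in energy prescription as well as in eating hours. Anyone reading a liver difference, or the lack of one, will want to know whether the arms ate different amounts and how precisely this was estimated. A wider interval than necessary makes that harder to judge. At stake are the precision of an adherence measure and the interpretation that leans on it.

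**Working it through.** **Inputs from the article (Sample size calculation):** 26 per arm, two-sided alpha 0.05, d = 0.80, stated power 0.8074866.

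**Assumptions (not in the article):** r = 0.2 to 0.7; a true intake difference of 0.5 SD; SD 500 kcal/day, used only to express interval widths in kcal.

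**1. The plan's own figure.** Noncentrality = 0.80 × √(26/2) = 2.8844. Critical t on 50 df = 2.0086. Power = 0.8075, as stated; 25 per arm gives 0.791, so 26 is the minimum. The present point does not affect this figure.

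**2. Precision of the intake contrast.** The t-test standard error is SD × √(2/26) = 0.277 SD, on 50 df. The ANCOVA standard error is that times √(1 − r²) × √(1 + 1/48), on 49 df; the second factor (1.010) is the cost of estimating the covariate slope. At SD 500 the t-test half-width is 2.0086 × 138.7 = 279 kcal.

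| r | SE ratio, ANCOVA to t-test | Half-width at SD 500 (kcal) | Narrowing | Power for 0.5 SD |
|---|---|---|---|---|
| t-test | 1 | 279 | – | 0.42 |
| 0.2 | 0.99 | 276 | 1% | 0.43 |
| 0.3 | 0.96 | 269 | 4% | 0.45 |
| 0.5 | 0.88 | 244 | 12% | 0.52 |
| 0.7 | 0.72 | 201 | 28% | 0.69 |

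The two methods break even where (1 − r²) × 49/48 = 1, that is r = 1/7, about 0.14.

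**3. Chance baseline difference.** With 26 per arm its standard deviation is 0.277 SD, so 95% of trials fall within ±0.54 SD. The part carried into an unadjusted on-diet comparison is r times that: ±0.16 SD at r = 0.3 and ±0.27 SD at r = 0.5. This assumes simple randomisation; stratifying by sex and BMI may reduce it.

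**4. Which r is relevant.** Here r is the correlation of baseline with the mean of the on-diet recalls. If any two recall occasions correlate by rho, then r = rho/√((1 + 2 rho)/3). So rho = 0.3 gives r = 0.41, and rho = 0.5 gives r = 0.61.

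**5. Which mean goes into the test.** The two sections quoted above define the intake mean differently, so the outcome must be fixed before the test. If a diet difference D exists only after baseline, the four-recall mean estimates (0 + D + D + D)/4 = 0.75 D, which is 25% too small. With D = 0.5 SD of one recall:

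| Analysis | Power, rho = 0.3 | Power, rho = 0.5 |
|---|---|---|
| t-test, four-recall mean including baseline | 0.49 | 0.39 |
| t-test, on-diet mean | 0.68 | 0.58 |
| ANCOVA, on-diet mean with baseline covariate | 0.75 | 0.77 |

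A simulation of 4,000 trials per setting gave 0.49, 0.68 and 0.76 at rho = 0.3, and 0.40, 0.58 and 0.77 at rho = 0.5.

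**The case against.** **The t-test is a legitimate choice.** In a randomised comparison it is unbiased and keeps its type I error. A reader might infer that chance baseline imbalance biases the result on top of the reported uncertainty. It does not: that imbalance is already part of the standard error. What remains is a conditional statement, that a baseline difference seen in this trial will sit partly in the unadjusted estimate.

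**Intake is an adherence measure.** A reader might infer that this contrast is what separates meal timing from energy restriction. No section gives it that role. Adjustment would not achieve it either, because on-diet intake arises after randomisation and the arms differ in both respects. This stands and limits the importance of the point.

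**The gain may be small.** It rests on a correlation that the article does not give. Baseline is a short recall over three days, and both diets are meant to change what people eat, so a low r is possible. At r = 0.2 to 0.3 the gain is 1% to 4%. Averaging several on-diet recalls raises r, as step 4 shows, but if rho is about 0.2 or less the gain stays small.

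**The 300 kcal figure is not an expected difference between arms.** A reader might take it as one. It is set against the control participant's energy requirement, and the fasting arm has no energy target, so the expected gap is unspecified. The power figures here therefore use an assumed difference in SD units.

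**The ANCOVA sentence might already cover intake.** The t-test sentence names no time point, and dependent variables is a broad term. Because intake has its own named test, this reading is possible but unlikely.

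**Conclusion.** The point holds as a minor matter of efficiency. The plan names an unadjusted test for intake, holds the baseline value, uses the better method for other variables, and gives no reason for the difference. With 26 per arm, adjustment narrows the interval by about 1% to 28% over the assumed r of 0.2 to 0.7. Power for an assumed 0.5 SD difference moves from 0.42 to between 0.43 and 0.69. Neither r nor an SD for intake is in the article, so the size within that range cannot be settled.

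The documents do not support calling the t-test invalid, and they do not support treating the intake contrast as the analysis that disentangles timing from energy. The stated sample size and the primary and secondary analyses are unaffected. The definition of the intake mean needs settling at the same time: averaging in the pre-diet recall shrinks the estimated difference by a quarter, and an adjusted analysis needs baseline kept out of the outcome.

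**What to change.** In the Statistical analysis section, replace the t-test for intake by ANCOVA of mean on-diet energy and nutrient intake on arm, with the participant's baseline intake as covariate. Report the adjusted difference with its 95% confidence interval, and show baseline intake descriptively by arm.

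In Assessment of dietary intake, define the on-diet mean from recalls during the intervention only and keep the baseline recall as the covariate. This agrees with the Compliance section and removes the conflict between the two.

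The cost is a sentence in each place and one error degree of freedom (49 instead of 50). No new data are needed. Participants without a baseline recall need the missing-data handling that the plan already applies to other variables. If r proves to be below about 0.14, the adjusted analysis is very slightly less precise than the t-test.

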### Study design

A diagram of the study design is demonstrated in Fig. 1. A flow chart of the study process is demonstrated in Fig. 2. A total of 52 patients with NAFLD will be screened based on the inclusion criteria. After participant recruitment from online advertisements and social media, 52 participants who meet the eligibility criteria will be enrolled for the trial. We used stratified block randomization with a block size of 2 Patients will be randomly assigned to either an intervention or control group based on BMI (25–30 and 30–35) and gender (male or female). First, we select patients who meet the criteria. Then that variable is used to match the next person with the first person. After all, two patients with similar characteristics are in the same block. Finally, two subjects in the same block are randomly assigned to either the IF diet or the low-calorie diet using random assignment software. All individuals who meet the inclusion criteria and voluntarily participate in the study will receive complete information regarding the purpose of the study, the type of intervention, and the duration of the study. Then, written informed consent will be obtained from individuals. The current clinical trial will be done based on the Helsinki Declaration. All participants will be informed that all services will be free of charge and that they can withdraw from the study at any time. Each person will be given a pre-made meal plan booklet with a set of menus and recipes for breakfast, lunch, dinner, and snacks based on the recommended diet.

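### Missing outcomes are to be handled by a linear regression method with no stated allowance for imputation uncertainty; read as single imputation, it inflates type I error if arm is modelled and shrinks the effect if it is not

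*Protocol article*

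**What the plan says.** The protocol article deals with missing data in one sentence under Statistical analysis: "Missing values will be treated according to the linear regression method". Three other statements in that section fix how it will work:

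- the analysis set: "The analyses will be performed based on the intention-to-treat (ITT) approach";
- the model: "ANCOVA with adjustment with baseline values will be used to assess the effect of intervention on dependent variables";
- the threshold: a p-"value < 0.05 will be considered statistically significant".

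The article does not say how many times values are imputed, which predictors are used, whether a residual is drawn, or how imputation uncertainty enters the standard error.

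Under Study design, participants are told that "they can withdraw from the study at any time". Under Assessment of hepatic fibrosis and steatosis, FibroScan is done once before and once after the intervention. A participant who leaves early therefore has only a baseline value of the primary outcome.

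**The concern.** A regression-filled value is a prediction from the other participants' data and carries no new information. An ordinary ANCOVA on the completed data cannot tell it from a measurement. Two things can go wrong, depending on whether arm is a predictor:

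- **Arm included.** Imputed points lie on the fitted surface. They add degrees of freedom without adding residual variation, so standard errors are too small.
- **Arm omitted.** Imputed points carry no arm difference, so they pull the estimated effect towards zero.

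At stake are the intervals and p-values of the primary FibroScan comparison and of any secondary ANCOVA with missing outcomes. The article leaves the imputation model open. If it is chosen after the data are seen, that choice can change the result.

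**Working it through.** **Inputs from the article (Sample size calculation).** 26 per arm, d = 0.80 (so SD = 1), two-sided test, "α err prob = 0.05", "Power (1-β err prob) = 0.8".

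**Assumed, because the article gives no figure.** 3, 5 or 8 of 26 missing per arm (12%, 19%, 31%), completely at random and equal between arms; normal outcomes; baseline–outcome correlation 0.5, with 0.7 as a check.

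**The plan's own figure.** Noncentrality 0.80 × √(26/2) = 2.8844, critical t on 50 df = 2.0086, power 0.80749. This matches the article exactly. The sample size calculation is not affected by this point.

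**Case A: fitted value imputed, arm in the model.** The imputed points lie on the fitted plane, so the effect estimate and the residual sum of squares equal those from the observed data. The residual df rise from m − 3 to 49 (m = number observed), and the variance factor for arm falls by about m/52. Hence

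reported SE / observed-data SE ≈ √((m − 3)/49) × √(m/52)

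- m = 46: 0.937 × 0.941 = 0.881
- m = 42: 0.892 × 0.899 = 0.802
- m = 36: 0.821 × 0.832 = 0.683

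Multiplying the nominal critical value of 2.010 (49 df) by these ratios gives effective cut-offs of 1.771, 1.611 and 1.372. Referred to t on 43, 39 and 33 df, they give type I error of about 8.4%, 11.5% and 17.9%.

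**Case B: fitted value imputed, arm omitted.** The imputed part contributes no arm difference, so the expected estimate is about 0.80 × (1 − missing fraction):

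- 0.80 × 23/26 = 0.71
- 0.80 × 21/26 = 0.65
- 0.80 × 18/26 = 0.55

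**Simulation** (correlation 0.5; 8,000 trials per setting for type I error, 4,000 for coverage at a true effect of 0.80):

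| | 12% missing | 19% missing | 31% missing |
|---|---|---|---|
| Type I error, fitted value, with arm | 8.6% | 12.0% | 19.0% |
| Mean reported SE / actual SD, with arm | 0.87 | 0.79 | 0.67 |
| Type I error, fitted value plus residual, with arm | 8.1% | 10.6% | 14.8% |
| Type I error, fitted value, without arm | 5.2% | 4.7% | 5.1% |
| Type I error, ANCOVA on observed values | 5.2% | 4.7% | 5.1% |
| Type I error, multiple imputation with arm, Rubin's rules | 5.1% | 4.6% | 4.6% |
| Coverage of 95% CI, with arm | 91% | 88% | 82% |
| Coverage of 95% CI, without arm | 93% | 89% | 78% |
| Coverage of 95% CI, observed values | 95% | 95% | 95% |

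Repeat runs gave 8.8–9.2%, 11.4% and 17.3–19.2% for the first row. Without arm, the simulated estimate was 0.70, 0.64–0.65 and 0.55, in line with Case B. With correlation 0.7 and 19% missing, type I error was 10.6% with arm and 4.5% without.

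**Does imputation gain anything?** At 19% missing and a true effect of 0.80, power was 82.3% for observed-value ANCOVA and 82.5% for imputation without arm. The 90.8% for imputation with arm comes from understated standard errors.

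**The case against.** A reader might infer that the plan prescribes filling each missing value once and analysing it as if observed, and that the 5% error rate is lost whatever the details. The article does not support that, for three reasons.

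- **Filling once is an inference.** Linear regression can also be the model inside a multiple imputation. "Statistical data will be analyzed using SPSS software version 22" does not settle the matter. A condensed article may leave the number of imputations, the predictors and the pooling rule to a fuller document that is not shown.
- **Inflation needs arm in the imputation model.** Without arm, and with equal missingness completely at random, the 5% level holds. The cost is then a shrunken effect and poor interval coverage, with no excess of false positives.
- **The size depends on dropout that the article does not give.** The right to withdraw shows that outcomes can be missing, but says nothing about how often. If none are missing, there is no harm.

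All three stand, and they limit how firmly the point can be put. They do not remove it. The article names a method, attaches it to ITT and ordinary ANCOVA, and mentions nothing that would carry imputation uncertainty into the result. Single imputation is the plainest reading, and both of its versions give wrong intervals at the planned effect once outcomes are missing.

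**Conclusion.** The point holds conditionally. If the sentence means single regression imputation and outcomes are missing, there are two possible results:

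- **Arm in the model:** reported standard errors are 13%, 21% and 33% too small at 12%, 19% and 31% missing, and type I error is about 9%, 11–12% and 17–19%. Drawing one random residual reduces this but does not cure it.
- **Arm omitted:** type I error stays at 5%, a true 0.80 SD effect is estimated at about 0.70, 0.65 and 0.55, and coverage falls to about 93%, 89% and 78%.

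It would go too far to say that every ANCOVA in the trial will be wrong, or that the stated 5% is lost in all cases. The figures rest on the assumed dropout, correlation and equal missingness completely at random. Informative or unequal dropout was not simulated. The plan should be changed, with moderate confidence, because the reading is the plain one but not the only one.

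**What to change.** Replace the missing-data sentence with one primary rule, for example:

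> The primary analysis is ANCOVA of observed 12-week values on arm and baseline value, with participants analysed as randomised; it is valid under missing at random. As a sensitivity analysis, missing 12-week values are multiply imputed (at least 20 imputations; model including arm, baseline value, sex and BMI stratum) and combined with Rubin's rules. No single-imputed data set is analysed.

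If the sponsor reads ITT as requiring every randomised participant in the primary analysis, the multiple imputation can be primary and the observed-value ANCOVA the sensitivity analysis. One of the two must be named before the data are seen. In the simulation both kept type I error near 5%.

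The cost is a short change of text, slightly more analysis work, and wider confidence intervals than single imputation would report. Both analyses assume missing at random, so neither protects against informative dropout.
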